## Record keeping of medication

The primary investigator, a sub investigator or a study nurse will keep record of medication and hand out medication when participants are present for the two-weekly control. Registration of medicine delivered from pharmacy, handed out to participants and unused medicine returned by participants will be executed.

Patients will be informed both orally and in writing to return all unused medication to the hospital and investigators. The primary investigator and study nurse will register used and unused medication and keep track of the ingested dose of each participant. The participant will also be asked to keep a journal of medicine intake. In cases where the amount of ingested medication is unclear, the highest certain dose ingested will be registered. In cases of lost medication or if the participant is unable to account for the medication, the ingested dose will be registered as null.

# Randomisation methods

The study is conducted as a randomised placebo controlled clinical trial, randomised in the ratio 2:1, rifaximin and placebo, respectively.

We expect no changes in clinical state, haemodynamics or other parameters in the patients receiving placebo, therefore we find it adequate to randomize in the ratio 2:1.

The study is dimensioned at including 32 patients in the rifaximin group and 16 patients in the placebo group.

The trial is a multi centre study, with seven hospital departments screening possible candidates for participation and referral to primary centre of investigation.

Packing and labelling will take place at the regional hospital pharmacy. Labelling will be performed after applicable legislation including name of pharmacy, trial name, patient name, CPR and trial number, dose, storage and contact information of principle investigator.

The randomization list in the ratio 2:1 will be produced electronically. This randomization list will be stored at the regional pharmacy. Only personnel at the pharmacy will know the randomisation code.

Participants will be assigned to a randomisation number electronically.

This two-digit trial number will henceforth identify trial participants.

The sponsor, principle investigator and sub investigators, nurses, laboratory assistants or personnel involved in the care for the trial participant will have no knowledge of the blinding. Coded envelopes with randomisation keys to each participant will be kept at Hvidovre Hospital in a safe and locked drawer. These envelopes will be available to sponsor and investigators at all times in case unblinding should be necessary.

## Disruption of blinding

Blinding will be disrupted if one of the following events occurs:

- A trial participant is admitted to hospital with a severe or life-threatening condition where rifaximin is contraindicated.
- A trial participant experiences serious adverse side effects or complications that could be caused by rifaximin.

If blinding is disrupted, the patient will be excluded from the trial.

# Establishment of a Bio bank

In connection to this study a research bio bank and a bio bank for future research will be established. The objective is that the bio banks will contain material from participants before and after trial medication. The material is full blood, EDTA plasma, urine, ascites and faeces samples.

In connection with liver vein catheterisation an amount of blood will be drawn for storage in a research bio bank, located at Department of clinical physiology and nuclear medicine, Hvidovre hospital.

The blood will be drawn during liver vein catheterisation from the same tube as the remaining blood samples and implies no further risks, side effects or nuisances to the patient. Urine samples are taken from the collection of 24-hour urine. Ascites is taken by diagnostic puncture.

The blood, urine and ascites is immediately preserved at a temperature of –80 degrees Celsius. These samples are stored at department of clinical physiology and nuclear medicine, Hvidovre Hospital.

Faeces samples from all patients will be stored at a temperature of –80 degrees Celsius at Statens Serum Institute.

## Aim of the bio bank

The established bio bank will have two sections and serve two purposes:

The research bio bank will contain blood samples that for various reasons are not ready for immediate analysis. These samples will be stored in a research bio bank during the trial course and analyzed for results during the trial period. This accounts for app. 10 ml of full blood. The blood will be used for cytokine analysis, bacterial DNA analysis and analysis for vasoactive hormones. Data from these samples will enter the database and registers of this trial, and excess blood from these analyses will be destroyed hereafter. This material is person attributable.

Second, a bio bank of full blood, plasma, urine, ascites and faecal samples for future research will be established. The material accounts for 30 ml of full blood at initiation and at the end of trial period and in total 20 ml of urine, 20 ml of ascites and 2 faecal samples. A part of this blood will undergo analyses for cytokines and bacterial DNA; the remaining blood, urine, ascites and faeces is stored for investigations that are not yet planned or initiated.

The aim of this bio bank is to contribute significantly to future research and thereby optimize treatment of liver cirrhosis. This material is person attributable.

All investigations and results derived from the bio bank for future research will serve the purpose of improving the life and health of patients with liver cirrhosis.

Permission from The Danish Data Protection Agency, Medical Products Agency and regional Science Ethics Committee will be obtained before initiation of this trial.

## Plans for the bio bank

Blood samples stored for later investigation in relation to this trial will be destroyed at the end of the trial. The primary investigator will store results of analyses until statistical processing. Storage of data, trial material and CRF’s will be kept in accordance to general guidelines for storage of person attributable material, set by The Danish Data Protection Agency.

The remaining blood and material stored for future research in the bio bank will be person attributable as well. No material stored in the bio bank will be exported to other hospitals, research facilities or to other countries.

When or if the material concludes in another study and future investigations, a new protocol and repeated registration at Data Protection Agency will be performed.

The blood will be stored for a period of 10 years after the end of this trial. Then the blood will be destroyed.

# Adverse events and side effects

## Definitions

An adverse event is: Any untoward medical occurrence in a patient or clinical trial subject administered a medicinal product and which does not necessarily have a causal relationship with this treatment.

A serious adverse event is: Any untoward medical occurrence or effect that at any dose results in death, is life-threatening, requires hospitalisation or prolongation of existing hospitalisation, results in persistent or significant disability or incapacity, or is a congenital anomaly or birth defect.

An adverse reaction is: Any harmful and unwanted reaction towards a trial drug irrespective of dose.

An unexpected adverse reaction is: Any harmful and unwanted reaction towards a trial drug, whose character or severity does not correlate to product information (investigators brochure).

These definitions regards to medical treatment, investigations and invasive procedures performed during the trial.

Events and reactions that will not be handled as serious adverse events:

- Adverse events and reactions that with certainty are occurring in relation to or are caused by the treatment and diagnosis of other medical conditions or diseases besides liver cirrhosis during the trial period will not be reported.
- Planned admission to hospital due to diagnostic procedures.
- Medical conditions that can be expected as complications to the underlying progressive liver cirrhosis will not be considered adverse events, serious adverse events or unexpected adverse reactions. That is, episodes of hepatic encephalopathy, variceal bleeding, hyponatriemia, SBP and infections related to liver cirrhosis, and hospitalisation due to any of these causes.
- Abnormal blood analyses that is regularly seen in patients with liver cirrhosis, such as a fall in albumin or platelet count or an increase in INR, P-bilirubin or P-ammonium levels.

In any questions of doubt regarding the above, investigators will inform sponsor and an assessment of possible causality will be performed.

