## Disruption of the trial

The entire trial will be disrupted prematurely if knowledge is obtained that suggests rifaximin is unsafe or indefensible to use in patients with liver cirrhosis.

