## Reporting of Suspected Unexpected Serious Adverse reactions (SUSAR’s)

Any serious adverse event that is assessed to have causal relation to the trial drug is a serious reaction. Unexpected serious reactions (not previously described in relevant product information(32)) are registered as SUSAR’s.

Sponsor will gather all relevant information about the SUSAR’s. In case of death or life threatening reactions The Danish Health and Medicines Agency will be informed within 7 days of sponsor’s knowledge of the reaction.

Within 8 days a report of sponsor and investigators follow-up on the incident will be forwarded. Reporting will be done electronically.

All other SUSAR’s will reported to The Danish Health and Medicines Agency within 15 workdays.

In case of a SUSAR sponsor and principle investigator will assess the consequences and impact of the event before unblinding. Hereafter unblinding will be performed before reporting to authorities. In the evaluation of possible SUSAR’s investigators brochure for Xifaxan 550 mg (provided by Norgine Denmark, see appendix) will be addressed.

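### The adverse-event definition contradicts itself on cirrhosis complications, and exit from the trial after unblinding is not reconciled with the planned intention-to-treat analysis

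*Protocol*

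**What the plan says.** **Adverse events.** The protocol's Definitions section (under Adverse events and side effects) opens with a broad definition of an adverse event: "Any untoward medical occurrence in a patient or clinical trial subject administered a medicinal product", whether or not treatment caused it. An event is serious if, among other criteria, it is fatal, life-threatening or leads to hospitalisation. A list then follows under the heading "Events and reactions that will not be handled as serious adverse events". Its third bullet covers conditions to be expected as complications of the disease and says that "complications to the underlying progressive liver cirrhosis will not be considered adverse events, serious adverse events or unexpected adverse reactions". It names "episodes of hepatic encephalopathy, variceal bleeding, hyponatriemia, SBP and infections related to liver cirrhosis, and hospitalisation due to any of these causes". Where there is doubt, the investigator informs the sponsor and causality is assessed.

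**Unblinding.** The section Disruption of blinding gives two triggers. One reads: "A trial participant experiences serious adverse side effects or complications that could be caused by rifaximin". The consequence is: "If blinding is disrupted, the patient will be excluded from the trial". Withdrawal of trial participants also lists a broken blind as a reason for withdrawal. The section on SUSARs has the sponsor and principal investigator assess the event while blinded, and then says: "Hereafter unblinding will be performed before reporting to authorities".

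**Related rules.** The whole trial stops early "if knowledge is obtained that suggests rifaximin is unsafe" (Disruption of the trial). The Statistics section plans intention-to-treat and per-protocol analyses using all available data, and no interim analysis. The dropout sections keep the data collected while the patient was in the study, unless erasure is requested, but plan no follow-up of dropouts.

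**The concern.** Keeping expected disease events out of expedited reporting can be defended. The third bullet does more: it takes them out of the adverse-event category altogether. An investigator who follows it would not enter an episode of SBP as an adverse event or complete a serious-event form for a bleed. One who follows the definitions above it would do both. Different investigators could code the same event differently, and the tables by arm would depend on who coded.

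Two things are at stake. The first is oversight during the trial. No interim analysis is planned, so serious-event reporting to the sponsor is the main running channel by which a safety signal could lead to early stopping, and the bullet takes these events out of it. The second is the analysis population. Leaving the trial because of a suspected serious reaction depends on what happened after randomisation. Unless such patients are explicitly kept in the analysis, the randomised comparison is weakened.

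**Working it through.** The protocol states no figure on this point, so the check sets its sections side by side.

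**1. Is Definitions consistent with itself?** The list heading limits the exemption to handling as a serious event. The bullet extends it to adverse events and unexpected reactions. The definition above the list has no exception for disease complications. These three statements cannot all hold. The bullet exempts hospitalisation for the named conditions but does not mention death or threat to life, which the serious-event definition includes, so those cases are left unclear.

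**2. What is captured by another route?**

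| Exempt event | CRF contacts (days 7-10, 14-17, 21-24) | Secondary outcomes | Register follow-up |
|---|---|---|---|
| Encephalopathy | as a complication | minimal form only | named |
| Variceal bleeding | as a complication | not named | named |
| SBP | as a complication | under infections | named |
| Other cirrhosis-related infection | as a complication | under infections | only if admitted |
| Hyponatraemia | only if noted as a complication | not named | not named |
| Admission for these | not named | named | named, with reasons |

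Mortality and comorbidity over six months are also a secondary outcome. Most of the exempt events can therefore be compared by arm as outcomes. Hyponatraemia is the one named condition that no outcome or follow-up list mentions.

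**3. When is it known?** Reporting of serious adverse events brings a serious event to the principal investigator or sponsor by the next working day. Follow up places the register collection one month after the last patient's last visit. Under the Time schedule, enrolment starts in November 2012 and follow-up ends in January 2016. For an early patient the register data could thus come about three years after the event.

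**4. What happens after unblinding?** Dropout means fewer than 32 tablets taken, or consent withdrawn. At two tablets a day, 32 / 2 = 16 days. A patient unblinded and withdrawn before that point is also a dropout, with data kept but no follow-up planned. A patient withdrawn later on treatment need not be a dropout, so the data-retention rule, which is written for dropouts, does not clearly apply. Follow up says patients are followed until death or end of trial, without saying whether withdrawn patients are included. Statistics promises intention-to-treat. No section says whether the day 29-32 measurements are sought in these patients.

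**5. Size.** The protocol gives no four-week rate for these events. As an assumption only, take a rate *p* in both arms and the planned enrolment of 38 and 19 (38 + 19 = 57). Expected patients with an event = *n* x *p*:

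| Assumed *p* | Rifaximin, 38*p* | Placebo, 19*p* |
|---|---|---|
| 5% | 1.9 | 0.95 |
| 10% | 3.8 | 1.9 |
| 20% | 7.6 | 3.8 |

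Counts this small mean that leaving out a few events would visibly change an adverse-event table. They also mean that no formal safety test would be strong under any coding. With the placebo rate at *p* and the rifaximin rate at 2*p*, exact Fisher power is about 1.5%, 10% and 28% respectively.

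**The case against.** The strongest reply is that the protocol captures these events, whatever they are called. Complications go on the case report form at three contacts. Infections and hospitalisation are secondary outcomes, and the register follow-up covers most of the rest in both arms. A need for other antibiotics, or encephalopathy above grade 1, leads to withdrawal, so the trial team learns of those cases as they occur. Doubtful cases go to the sponsor, and the stopping rule acts on any knowledge obtained, not only on serious-event forms. All of this stands. It rules out the claim that the safety comparison loses these events.

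Other stronger readings also go beyond the text:

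- *A fatal SBP or bleed is never a serious event.* The bullet does not mention death and the serious-event definition does. This is an ambiguity, not a stated rule.
- *The bullet breaches the rule that all adverse events are registered.* If an event is not an adverse event, that rule is not engaged. The contradiction lies within Definitions.
- *Rifaximin patients are selectively removed.* Suspicion is judged blind, so a placebo patient with the same event is treated alike. Imbalance would arise only if rifaximin does cause such reactions.
- *Intention-to-treat is broken.* Leaving the trial is not deletion of data, and the triggering reaction is itself recorded and followed. Detailed analysis sets may properly be left to a statistical analysis plan.
- *About 30% of patients would be affected.* That Background figure concerns infection in patients who are being or have been admitted. This trial excludes patients with signs of infection or recent antibiotics and treats mainly outpatients for about four weeks. It cannot serve as a rate here, and shifts in percentage points worked out from 16 placebo completers do not measure the effect either.

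The reply does not remove the contradiction in Definitions, the gap in prompt reporting, or the unreconciled exit rules.

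**Conclusion.** The concern holds in a limited form. Definitions contradicts itself. If the bullet is followed as written, the adverse-event and serious-event tables by arm, and prompt reporting to the sponsor, omit the named cirrhosis complications. Most of them are recoverable from other data, but the register part comes only at the end of the trial, and hyponatraemia has no named place in any outcome or follow-up list.

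Separately, the rule that unblinded patients leave the trial is not reconciled with the intention-to-treat analysis of all available data, or with the absence of planned follow-up for dropouts.

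No numerical effect can be claimed. The counts above rest on assumed rates and show only that few events are expected. The conclusion assumes that investigators would apply the bullet literally and that Appendix 6, which is not shown, does not restore adverse-event coding for these conditions.

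**What to change.** 1. In Definitions, align the third bullet with its heading and with the definitions above it. State that the named complications are recorded in the case report form and tabulated by arm as adverse or serious adverse events. State that fatal and life-threatening cases are reported to the sponsor, and that the exemption covers expedited reporting only. This also gives hyponatraemia a place in the record.
2. Reconcile Withdrawal of trial participants, the dropout sections, Disruption of blinding and Statistics. State that unblinded or withdrawn patients stay in the intention-to-treat and safety sets with their available data, and say whether Follow up applies to them. This concerns data and analysis only, not whether such a patient continues trial medication.

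The cost is protocol wording and a few more event forms in 57 planned patients treated for about four weeks. No change to sample size or visits is needed.

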## Registration of adverse events / adverse reactions

Investigator and sponsor has in the enclosed statement obliged to comply with protocol, including to report all adverse events, serious adverse events and suspected unexpected serious adverse reaction to relevant authorities as outlined by the Danish Health and Medicines Authority(37) and The European Commission(38).

AE and SAE’s: At every contact, both by telephone and in person, the participant will be asked if adverse events have occurred since the last contact. All adverse events is registered in the Case report Form. Serious adverse events are also registered on the SAE form included in Trial Master File. All adverse events will be followed until stabilisation, termination or decision of causality.

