## Follow up

A register based follow up on patients through medical records will be performed at the end of trial, which is 1 month after last patient’s last visit. Data collection will be limited to hospital admissions and reasons hereto, complications to liver cirrhosis (esophageal bleeding, spontaneous bacterial peritonitis, hepatic encephalopathy and hepatorenal syndrome), and mortality and reasons hereto.

Hence, patients will be followed up until death, or end of trial.

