## Reporting of serious adverse events

Information on all serious adverse events is registered in the SAE form included in Trial Master File. All serious adverse events is reported to principle investigator ([name]) or Sponsor ([name]) no later than first coming workday after investigator has become aware of the event. The immediate report will be followed by a detailed written report within 24 hours. Adverse reactions, that are not life threatening and mild in character, do not require medical attention or intervention and are insignificant to the patients’ further involvement in this trial will not be reported to sponsor. These will be registered in case report forms and available to monitoring units and sponsor at any time.

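### Follow-up of an adverse event may end once causality has been decided, even if the event is neither resolved nor stable

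*Protocol*

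**What the plan says.** The rule stands in the protocol under Registration of adverse events / adverse reactions: "All adverse events will be followed until stabilisation, termination or decision of causality". It covers all adverse events, with no separate provision for serious or drug-related ones.

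Four other parts of the protocol bear on how long an event is watched:

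- **Reporting of serious adverse events.** A serious event is reported promptly, and then: "The immediate report will be followed by a detailed written report within 24 hours". No later report on its outcome is mentioned.
- **Reporting of SUSARs.** Classification depends on causality: "Any serious adverse event that is assessed to have causal relation to the trial drug is a serious reaction". For SUSARs, "Sponsor will gather all relevant information about the SUSAR’s", and, after the sentence on fatal or life-threatening reactions, "Within 8 days a report of sponsor and investigators follow-up on the incident will be forwarded".
- **Follow up.** Medical records are reviewed at the end of the trial, one month after the last patient's last visit. The scope is restricted: "Data collection will be limited to hospital admissions and reasons hereto, complications to liver cirrhosis", plus mortality and its causes. On duration: "Hence, patients will be followed up until death, or end of trial".
- **Disruption of blinding.** Serious side effects that rifaximin may have caused are one trigger for breaking the blind, and then: "If blinding is disrupted, the patient will be excluded from the trial".

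The section on following up possible dropouts adds that no follow-up of dropouts is planned. The section on data registration for dropouts does seek mortality and any morbidity that explains the dropout.

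**The concern.** Two of the three end points describe the event: it has ended, or it has become stable. The third describes a decision by the investigator or sponsor. Deciding whether the drug caused an event does not show whether the patient has recovered. Because the end points are joined as alternatives, reaching that decision is enough to stop following an event that is still active.

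At stake is the record of outcome, duration and later course for events closed in this way, and with it part of the protection owed to a patient whose event is continuing. The protocol itself gives a reason for wanting the later course: its section on possible side effects notes that symptoms reported with rifaximin resemble those of the underlying cirrhosis. An early view on causality may therefore be uncertain, and what happens next is relevant evidence.

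This is a rule that the protocol states and states badly. It is not a detail that could be left to an analysis plan.

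**Working it through.** No arithmetic applies, since the point depends on wording and not on any figure. The check is whether another part of the protocol requires follow-up to outcome and so overrides the rule.

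1. **The rule itself.** The end points are alternatives. Nothing says that the latest of them governs, and serious or related events are not excepted. Early closure is permitted, though not required.

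2. **Serious event reporting.** The duties are a prompt report and a written one within 24 hours. Both concern notification, and neither extends to the outcome.

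3. **SUSAR reporting.** Gathering information and sending a follow-up report within 8 days both continue the work on an event after it has been judged related. But they apply only to SUSARs, and the report is bound to a time and not to resolution. A serious reaction that is related but expected is not a SUSAR, so it falls outside these duties.

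4. **Scheduled contacts.** There are telephone contacts at days 7-10 and 21-24, a clinic visit at days 14-17 and readmission at days 29-32. The first three register side effects, complications and wellbeing, and the readmission repeats the clinical examination. At every contact the patient is also asked about adverse events since the last one. These contacts would reveal most later worsening while the patient remains in the trial. They do not oblige anyone to follow an event still open at the last contact.

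5. **Record review.** Admissions with reasons, named cirrhosis complications, and deaths with reasons are found up to the end of the trial. The outcome of an adverse event that led to none of these is not on the list.

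6. **Patients who leave.** Withdrawal criteria include a need for other antibiotics, certain admissions, unblinding and worsening encephalopathy. An unblinded patient is excluded, and a patient who has taken fewer than 32 tablets (16 days of treatment) counts as a dropout, for whom no follow-up is planned. Scheduled contacts may therefore stop for just those patients whose blind was broken over a suspected drug reaction. The Follow up section speaks of following patients until death or end of trial, and does not say how this fits with the statement on dropouts.

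No section overrides the rule. Items 3 to 5 narrow its effect, and what they leave uncovered is:

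- events without admission that are still open at the last contact;
- serious reactions that are related but expected;
- events in patients who were withdrawn, unblinded or dropped out.

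**The case against.** The strongest reply is that the wording hardly matters, because the remaining procedures catch what is important. Patients are contacted or seen four times after treatment starts. Death and hospitalisation, which are among the main ways in which an event becomes serious under the protocol's definition, are found in the record review. SUSARs receive further work. This stands as a limit on the consequence, but it does not reach the three groups listed above.

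The case report form, the form for serious events and the authority guidance to which the protocol binds the parties are not shown, and any of them may require an outcome and end date. This also stands: none of them can be called deficient, and the point concerns the protocol sentence alone.

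A reader might be tempted to infer more. The documents do not support these four readings:

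- **That follow-up of the gravest events ends within days, because fatal or life-threatening SUSARs must be reported within 7 days.** These are the events for which the protocol also requires information gathering and an 8-day follow-up report. In fatal cases the outcome is already known.
- **That serious events suffer most because their causality is decided fastest.** Apart from the SUSAR reporting clocks, the protocol gives no timing for the causality assessment.
- **That a causality judgement is never revisited.** Nothing forbids updating it. The text only fails to require the follow-up that would inform an update.
- **That the safety comparison between arms is compromised.** Adverse events are not among the listed outcomes, and the protocol plans no comparison of event duration or resolution. The count of registered events does not depend on when their follow-up stops.

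**Conclusion.** The point holds as a defect in one stated rule. A causality decision alone may end the follow-up of any adverse event that is neither resolved nor stable, and nothing else in the protocol requires follow-up to outcome.

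The consequence is modest. The exposure lies mainly in the three groups identified above. Its size in events cannot be derived, because the protocol gives no expected rate of adverse events and no timing for causality decisions in general.

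The conclusion assumes that the sentence is applied as written and that the forms and guidance not shown add no outcome requirement. If they do add one, actual practice may be sound, but the protocol sentence would still conflict with it. The correction is inexpensive and worth making, and the trial's efficacy conclusions do not depend on it.

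**What to change.** Delete the causality decision as an end point in Registration of adverse events / adverse reactions, so that every adverse event is followed until it has resolved or stabilised, whatever the judgement on causality.

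Reconcile that sentence with Follow up of possible dropouts, Data registration on dropouts, Follow up, Disruption of blinding and the SUSAR section, so that it is plain that open events are also followed in patients who are withdrawn, unblinded or dropped out, within the limits of their consent. Check that the case report form and the form for serious events match the revised sentence.

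The cost is one clause, the cross-references to it, and a few more telephone or record checks for events still open when scheduled contacts end. No visit or invasive procedure need be added.
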